### Secondary outcomes

#### Feasibility and utility of implementation facilitation

##### Focus groups

We will invite all teachers of senior elementary students to participate in a focus group at each intervention school at the end of the school year, for each year of the intervention. A single discussion will be held at each school at a convenient time (e.g., lunch break). We estimate 85% of teachers will participate, based on previous school research. We will ask teachers about their experiences with the intervention and the implementation supports, including their perceptions of effectiveness. We will also ask about any feedback they have on the interventions and their delivery. Discussions will be approximately 30 min in duration and will be conducted by research staff trained in facilitating focus groups. Teachers will provide informed consent prior to participation. Students from four randomly selected intervention classes will be recruited to participate each year of intervention implementation (approx. *n* = 160, 6–9 students per group). All students with parental consent/student assent who are present on the day will be invited to participate for approximately 30 min. We will ask students about their perceptions of the interventions, including satisfaction. To maintain confidentiality, no identifying details will be collected. Focus groups will be conducted at the end of each the school years by research staff trained in facilitating focus groups (including previous work with children). Finally, we will invite members of the 3-PLT to participate in focus groups and provide feedback regarding barriers and facilitators to implementation, and suggestions for how the implementation process can be improved.

##### Teacher surveys

Each spring (April–May), we will open an online survey to examine school climate from teachers’ perspectives. The survey will consist of items drawn from the teacher and staff version of the Delaware School Climate Survey (Bear, Gaskins, Blank, & Chen, 2011), which covers perceptions of safety, student behavior, and overall climate. In the original student school climate survey, researchers conducted a multigroup confirmatory factor analysis and identified multiple specific factors associated with school climate, including teacher-student relationships, school safety and liking school, using this brief, psychometrically sound scale (Bear et al., 2011). In addition, we will adapt violence and mental health items from the MiPHY to reflect teacher perceptions of the prevalence and severity of violent behaviors and mental health problems among their student populations. All teachers will be notified of the survey during a staff meeting. Reminders will be sent by the 3-PLT until a 75% response rate has been achieved.

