To inform the optimal implementation strategies for these effective interventions, we develop and test an intervention focused on promoting a positive school climate guided by a school-based 3-person leadership team (3-PLT) using a hybrid Type II design. A hybrid Type II design tests the effectiveness of the intervention and determines the feasibility and potential utility of an implementation strategy (Curran, Bauer, Mittman, Pyne, & Stetler, 2012). The 3-PLT includes representatives from the police (School Resource Officer, SRO), school (e.g., administration), and mental health services (i.e., social work), the latter of whom leads the team as a newly appointed climate specialist (CS). The team, led by the CS, work together to support the integration of the key intervention components: (1) RJ practices, (2) MHFA training, and (3) CPTED (see Fig. 1). The CS coordinates these efforts as a staff member within the school through a process of interactive problem solving and supports, consistent with the implementation facilitation strategy (Ritchie, Dollar, Kearney, & Kirchner, 2014). We will focus on change among students in an early developmental period—elementary school students aged 8–12 years—in a county with significant social and economic challenges. The purpose of this research is to study the effectiveness and implementation of three complementary interventions delivered concurrently to enhance school safety through improved school climate. School climate represents a critical mechanism by which interventions, including multicomponent school safety and mental health interventions, can reduce risk of violence and mental distress among youth.

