### Methods

The cluster randomized trial evaluates a school safety intervention in a community with significant need, Genesee County, Michigan (see Fig. 2). This study was reviewed and approved by the Michigan State University Institutional Review Board (IRB# × 15-1129e). This study takes advantage of ongoing partnerships with the Genesee Intermediate School District in Michigan. We do not intend to collect data from participants who discontinue or deviate from protocols. Among the primary data sources to be collected (e.g., focus groups, interviews, teacher surveys), the data will be kept on a password protected server and de-identified. The study does not employ a data monitoring committee, but this study is structured such that the intervention team (i.e., employees of the GISD), is separate from the training team (i.e., employees of international and regional organizations, local universities, and the district wide [GISD] training team offering training in facets of the intervention), which is separate from the data collection team (i.e., employees of the two universities charged with the process and outcome evaluation, led by a co-PI), which is separate from the data analysis team (i.e., employees of the two universities charged with the process and outcome evaluation, led by a separate co-PI), providing sufficient independence and protecting against potential conflicts of interest. Thus, those tasked with training and technical assistance associated with components of the intervention are not involved in the analysis of data or reporting of outcomes given the potential bias this might engender as a result of the incentives associated with reports of a positive programmatic impact, such as profits associated with increased demand for training and technical assistance in the components of the program. There is no similar financial incentive for university-based researchers charged with the analysis of data and reporting of results, as they are not employed by any of the organizations charged with program implementation (i.e., GISD) or future dissemination of intervention components (i.e., training and technical assistance providers).

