### Evidence-based interventions to be implemented

#### Universal and targeted prevention

*Universal strategies* address an entire population regardless of risk level or current behavior. This approach aims to reach a large number of individuals at once; it develops strategies and a supportive environment that enables all children to achieve sufficient competence to thrive, and thus prevent or reduce engagement in violence (Leshner, 1997). In contrast, *targeted strategies* are designed for individuals who meet specified risk criteria, for example, showing signs of mental illness (Leshner, 1997). Simultaneous deployment, particularly one tailored to a school’s culture, is commonly considered more likely to effect change (Bonell et al., 2010; Maddox & Prinz, 2003). The proposed intervention incorporates universal and targeted approaches facilitated by a school-based 3-PLT. The team will participate in ongoing activities and engagement with school staff and students to support and reinforce the interventions, foster school-community relationships and support sustainability. These activities will be led by the CS who will apply principles of implementation facilitation to promote effective EBI delivery and tailor the interventions to the context.

The universal and targeted prevention design reflects the integrated and comprehensive intervention and suggested best practice, i.e. is comprehensive, improves access to mental health, balances physical and psychological safety, employs a positive school discipline approach, considers and responds to each schools’ culture and context, and acknowledges that change takes time (PriCowan et al., 2013). Prior school safety interventions have tended to implement these strategies in isolation rather than integrating in a coordinated manner. The proposed research will advance comprehensive school safety and using of implementation science to enhance delivery of such programs.

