**Fig. 3 Fig3:**
[figure not shown]
Implementation facilitation guided by the iPARHIS framework (Harvey & Kitson, 2016), adapted

Although the 3-component intervention approach is consistent across schools, approaches to integrating the EBIs will be tailored, making complete standardization neither feasible nor desirable. The proposed study will include development of an implementation guide as part of the Facilitation implementation strategy. The implementation guide will provide scaffolding for the CS to work with the other 3-PLT members and school staff to integrate the interventions into each school setting. The guide will provide specific steps in delivering the EBIs across sites, but will allow for tailoring of the interventions (innovations) to meet the needs of the schools (context), their staff (providers) and their students (recipients) (Bonell et al., 2010; Patton, Bond, Butler, & Glover, 2003; Toumbourou et al., 2007); we therefore seek to evaluate district-wide (yet individualized) implementation of the three school safety components.

The CS, in collaboration with the 3-PLT will be provided with a comprehensive set of resources and training for components of MHFA, RJ, and CPTED. The 3-PLT will be trained to deliver MHFA training to all school staff, deliver restorative justice efforts (e.g., be trained in peer mediation and similar restorative processes and facilitate this within schools), and liaise with expert consultants of environmental design. Environmental design components will be tailored for each school’s unique physical and social structures; in general, aspects of the school’s image/management, and increasing ownership of undefined spaces will be emphasized. The CS will coordinate activities and efforts between the 3-PLT, school staff, parents and youth. The CS will also develop processes based on local evidence. These processes will aid in informing refinements to the implementation guide that will support program fidelity while guiding customization of adaptable elements, and long-term sustainability.

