### Analysis

Our primary hypothesis is that students in schools receiving the intervention will report less violence (over time) compared to students in the control group. We also hypothesize that the intervention schools have an overall lower rate of violence over the school year compared with control schools. We expect that using implementation facilitation led by a climate specialist as part of a 3-person leadership team is a feasible and sustainable approach to integrating and effectively delivering the three intervention components. Finally, we expect that students in the intervention schools will report more positive school climate compared with those in control schools and that this, in turn, will result in lower improved mental health outcomes.

A cluster randomization design is proposed with random assignment by school to one of two arms: intervention or control. Evaluation of effectiveness outcomes will involve testing at four time points: a fall of Year 1, spring of Year 1, fall of Year 2, spring of Year 2. Measures will include school records and self-report data from students and teachers. The survey of students makes use of currently collected MiPHY data. Ten schools will be recruited in the first year and 10 in the following year; staggered recruitment will allow some initial evaluation testing of the program and allow the earliest possible start time with a number of schools. Including 20 schools in the research provides an opportunity to examine school level differences. To adjust for bias introduced by multiple comparisons across our outcome variables, we will use a pair of conservative (Tukey and Bonferonni) *p*-value adjustments in addition to reporting direct effect sizes (e.g., group differences in means) to allow for assessment not dependent on standard null hypothesis testing.

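### Teacher-survey reminders are assigned to the team that delivers the intervention, against the protocol's stated separation of intervention and data collection; if control teachers are surveyed, reminder effort appears to differ by arm

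*Protocol article*

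**What the plan says.** The Teacher surveys section describes an online survey opened each spring. On notification it says: "All teachers will be notified of the survey during a staff meeting". On follow-up it says: "Reminders will be sent by the 3-PLT until a 75% response rate has been achieved". No other sender of reminders is named.

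The 3-PLT (School Resource Officer, administrator and climate specialist) is part of what is being tested. The section on universal and targeted prevention says: "The proposed intervention incorporates universal and targeted approaches facilitated by a school-based 3-PLT". The text below Fig. 3 adds: "The 3-PLT will be trained to deliver MHFA training to all school staff". It gives the team the restorative justice work as well.

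The Methods section sets out a chain of separate teams: intervention, training, data collection and analysis. The third link reads: "which is separate from the data collection team (i.e., employees of the two universities charged with the process and outcome evaluation". The same passage notes that there is no data monitoring committee and offers the separation as the protection against conflicts of interest.

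Table 2 lists the teacher survey as a measure of school climate and of how effective staff believe the programme to be, with violence as the example. The Teacher surveys section adds adapted items on violence and mental health among students. In the section on the two-arm analysis the protocol states: "Measures will include school records and self-report data from students and teachers".

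**The concern.** Following up non-responders is part of data collection. Here it is given to the people whose programme the survey asks about, one of whom is a school administrator. A teacher who is reminded by that team, and who knows it is working towards a response target, may feel some pressure to answer, and to answer kindly. The separation described in Methods is meant to prevent this.

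A second issue depends on who is surveyed. Control schools get usual practice (Primary study aim), or no programme (Cost-benefit analysis). They therefore appear to have no 3-PLT. If their teachers are surveyed too, the stated procedure chases non-responders in one arm and names nobody to do so in the other. A comparison of teacher-reported climate or violence between arms would then rest on respondents recruited with unequal effort.

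**Working it through.** The protocol gives no figure to reproduce here. The 75% is an operational target with no derivation. The check is one of consistency, followed by an illustration.

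**Step 1: the conflict over who collects data.** Methods places data collection with employees of two universities, apart from the intervention team, which it labels as GISD employees. Teacher surveys gives reminders to the 3-PLT. Whether or not every 3-PLT member is employed by GISD, the team consists of a police officer, a school administrator and a mental health professional working in the school. It is not the university team. This conflict holds whichever schools are surveyed.

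**Step 2: what the team is prompting staff to rate.** Table 2 and the Teacher surveys section give climate, violence, mental health and perceived programme effectiveness. By contrast, the teacher and student focus groups are run by trained research staff, so the protocol applies a safeguard there that the survey reminders lack.

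**Step 3: are control teachers surveyed?**
- For: the notification sentence covers all teachers with no restriction by arm. The Focus groups section, when it means one arm, says so: "focus group at each intervention school at the end of the school year". The Analysis section names teacher self-report among the measures of a two-arm design.
- Against: Table 2 lists the survey only under feasibility of implementation facilitation and in spring only, whereas effectiveness is to be tested at four time points. The Implementation outcomes section plans a descriptive analysis.

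On balance it is likely that control teachers are surveyed, but this is not stated.

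**Step 4: would reminder effort differ by arm?** Only if Step 3 is answered yes and control schools have no 3-PLT. The second condition is strongly implied by the control condition, and by the Background's description of the climate specialist's post as new, but it is not written out.

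**Step 5: illustration of non-response bias, on assumed inputs.** Let r be the response rate and g the mean of responders minus the mean of non-responders, in SD units, taken as equal in both arms. The respondent mean differs from the mean of all teachers by (1 − r) × g. With intervention response 0.75 and control response r_c:

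bias in (intervention − control) = 0.25g − (1 − r_c)g = −(0.75 − r_c) × g

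| Assumed r_c | 0.75 − r_c | Absolute bias, g = 0.2 | Absolute bias, g = 0.5 |
|---|---|---|---|
| 0.75 | 0 | 0 | 0 |
| 0.65 | 0.10 | 0.02 SD | 0.05 SD |
| 0.55 | 0.20 | 0.04 SD | 0.10 SD |
| 0.45 | 0.30 | 0.06 SD | 0.15 SD |

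Neither r_c nor g is in the protocol. The sign follows g: if responders are the more favourable teachers, the bias works against the intervention; if they are the less favourable, it works for it.

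**The case against.** The strongest reply is that this is a small inconsistency in a minor measure. The research team opens the survey and the 3-PLT only sends reminders; nothing gives it access to answers. Methods draws its own conclusion narrowly: those who provide training and technical assistance stay out of analysis and reporting, and a reminder breaches neither. No comparison of teacher responses between arms is specified, whereas for the school discipline records the protocol says explicitly that the arms will be compared. The Mechanisms section raises teacher perceptions of climate only as a possible indirect influence, and the mechanisms row of Table 2 uses the student survey. Reminder arrangements for control schools may also be set out in a fuller protocol.

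Most of this stands, and it limits the point. It does not remove the conflict: Methods separates the intervention team from data collection as well as from analysis, and a reminder needs no access to answers to influence how people respond.

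A reader might infer that the arrangement biases the trial towards the intervention by a sizeable share of the standardized effect of .27 in the power section. The documents do not support that. The response gap and the responder difference are assumed, equal response gives no bias, and the formula in Step 5 turns against the intervention when responders are the more favourable. The .27 was also derived for 60 students per school, so it is no yardstick for teacher data.

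**Conclusion.** The point holds in a limited form. The assignment of reminders to the 3-PLT contradicts the separation claimed in Methods, and this rests on the text alone. It leaves a risk of socially desirable answers on items about the team's own programme; the protocol gives no means of sizing that risk.

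That reminder effort differs by arm is a reasonable inference, conditional on control teachers being surveyed and on control schools having no 3-PLT. If only intervention schools are surveyed, that part falls away and the conflict over separation remains. The size and direction of any non-response bias cannot be determined from the documents; the values in the table only show how it would depend on the assumptions.

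The consequence is confined to a secondary measure with a descriptive analysis planned. A reader might infer that the primary violence results are compromised. They are not: those outcomes come from the student MiPHY survey and the School Information System, and the reminders touch neither. The change is still worth making, because it is cheap and the protocol leans on the separation for its independence.

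**What to change.** Replace the reminder sentence with one stating that the university data-collection team sends identical reminders, on one central schedule and to the same 75% target, in all surveyed schools in both arms, with no 3-PLT involvement. State which schools are surveyed, and report response by arm.

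The cost is about one protocol sentence, since the survey is already online. The downside is a possibly slightly lower response in intervention schools, where a colleague's prompt may work better than a central message. If the present arrangement is kept, the statement in Methods should at least be corrected to say that the intervention team has a part in survey follow-up. That would remove the contradiction but not the risk.

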##### Mechanisms

We will assess potential mechanisms by which participation in the intervention influences secondary student outcomes including emotional functioning (anxiety and depression symptoms, wellbeing) using items from the MiPHY survey (Michigan Department of Education, 2016). Specifically, we will examine if school climate mediates the relationship between intervention participation and school climate; school climate will be assessed using items from the Delaware survey (Bear et al., 2011). School climate serves as a critical intermediary between the intervention components and student mental health and safety experience. Collectively, the interventions are thought to improve positive perceptions of school climate across constituents – students, teachers, school staff and administrators. Students and teachers often have different perceptions of the same objective experiences. Although there is a clear link between student climate perceptions and positive student outcomes (Esposito, 1999; Haynes, Emmons, & Ben-Avie, 1997), there may be indirect influences on student outcomes through *teacher* perceptions of climate. Teachers who perceive poorer school climate report higher job-related stress and poorer teaching self-efficacy (Collie, Shapka, & Perry, 2012), which in turn can influence student outcomes. We assess climate holistically to understand how stakeholders across the school may influence ultimate student outcomes.

##### Cost estimates

We will estimate the resources required for the intervention and its implementation and estimate the net costs using a resource-based costing approach. We will track activities relevant to site replication or implementation costs, versus intervention development and research costs because only the former would be required of other sites who might adopt the intervention program (Hurley & Matthews, 2007; Neumann, Sanders, Russell, Siegel, & Ganiats, 2016). Specifically, we consider implementation costs to be those costs associated with replication that would be required by those adopting the program (Neumann et al., 2016). This would include components of the intervention that require tailoring for replication, recruitment or promotion costs to engage practitioners and participants, and training, supplies and labor costs for evaluation as indicated (Ritzwoller, Sukhanova, Gaglio, & Glasgow, 2009).

